### Interim analysis

The AFFELECT trial is deemed a low-risk trial and no independent safety monitoring board was established based on prior evaluation and ethical committee decision. However, continuous monitoring for serious adverse events (thromboembolic events and hospitalizations due to heart failure) is applied.

A statistical interim analysis for serious safety events was performed in March of 2023 by an independent statistician from Tampere University, 5 weeks after the randomization and obtaining first month follow-up data of 200 patients comparing the risk of cardiovascular hospitalizations blinded to the group allocation. No statistically significant association was found, and the study was continued as planned.

### Sample size calculations and considerations

The power calculation indicated that 500 randomized patients are required to ensure 90% power (one-sided alpha level of 0.025) to reliably demonstrate non-inferiority, should the elective treatment prove inferior with respect to the primary end-point. The experimental treatment (elective approach) will be considered inferior if the lower bound of the 95% confidence interval for the difference in sinus rhythm prevalence (elective minus acute) falls below −10%. The calculation is based on the assumption that the prevalence of sinus rhythm in the control population is 90%. A 10% margin in sinus rhythm prevalence between the treatment groups is deemed clinically acceptable, as the prevalence of sinus rhythm can fluctuate daily among patients, and a variation of less than 10% is unlikely to affect the long-term prognosis of the participants. If patients were randomized into two equal groups, the total sample size would be 380 patients. However, a 2:3 randomization ratio was chosen to conservatively account for the anticipated occurrence of unplanned early CV in the delayed strategy group, which would lead to exclusion from the per-protocol population, as patients were informed about this possibility prior to randomization. For every patient randomized to the acute CV treatment group (at least 190 patients), three patients will be randomized to the elective CV treatment group (at least 285 patients). This randomization ratio accounts for the possibility that up to one-third of patients may request more urgent CV after randomization (with no unplanned CVs for unbearable symptoms the minimum number of patients would be thus 190 + 190 patients). This assumption was based on previous findings from the FinFib study, which indicated that up to one-third of patients undergoing emergency CV experience symptoms severe enough to interfere with daily life (EHRA Class III–IV)^6,20^ and therefore they might need an earlier CV. Considering the potential loss of patients to follow-up, the study aims to recruit approximately 5% (25) more participants than the minimum required by the power calculations (475 patients), resulting in a total of 500 patients.

Statistical analyses will be performed by the investigators in collaboration with an independent statistician from Tampere University who is not involved in data collection. Established statistical methods are employed to compare the differences between groups. χ^2^ testing is used to compare the distributions of categorical variables, while parametric testing methods, as *t*-test, are applied to normally distributed continuous variables. Non-parametric testing methods are used for variables not following normal distribution.

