**Conclusion:**

The AFFELECT trial tests whether delayed management of recent-onset AF/AFL is a non-inferior alternative to acute CV, aiming to reduce ED burden, number of needed CVs, and redirect care to specialized arrhythmia units.

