### Randomization

Patients are randomized either to acute CV (standard treatment) or to delayed (elective) CV with a randomization ratio of 2:3. The ratio is balanced to favour delayed CV with the a priori assumption that up to one in three patients in the delayed CV group may require expedited CV^6,20^ (i.e. before the intended waiting period of 5–9 days) for symptom relief. Randomization is performed in site-specific blocks with the intention of balancing patient randomization if the number of patients is low in any given participating centre (block size is blinded until the end of the trial patient enrollment). Randomization is performed through a dedicated website accessible by centre-specific user IDs and passwords. The group allocation is not blinded.

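### The only decision rule labels the elective approach inferior whenever the lower 95% bound is below −10%, so failing to show non-inferiority counts as inferiority and no inconclusive result is possible

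*Protocol article*

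**What the plan says.** The article presents a non-inferiority trial; its abstract concludes that the trial "tests whether delayed management of recent-onset AF/AFL is a non-inferior alternative to acute CV". The purpose, design and conclusion sections use the same framing.

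The only rule that turns the primary result into a verdict is in Sample size calculations and considerations: "The experimental treatment (elective approach) will be considered inferior if the lower bound of the 95% confidence interval for the difference", taken as elective minus acute, is below −10 percentage points. The rule sets no condition on the upper bound. No other section names a result in which non-inferiority is simply not demonstrated.

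The same section gives the design basis: "90% power (one-sided alpha level of 0.025"), and the assumption that "the prevalence of sinus rhythm in the control population is 90" per cent. It describes a 10% margin as clinically acceptable. Its preceding sentence also uses the word loosely: it describes power to show non-inferiority in the event that the elective treatment turns out inferior, whereas such power is computed for a treatment that is not worse by the margin.

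**The concern.** With elective minus acute as the difference, a lower bound below −10% says only that a deficit of more than 10 points has not been excluded. It does not say that elective care is worse. In the ordinary sense that needs an upper bound below 0.

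A three-way reading is therefore needed: non-inferiority shown, non-inferiority not shown, and elective worse. The rule collapses the last two.

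At stake is the reported verdict when the interval spans both −10% and 0. Such a trial has not settled the question, but under the written rule it would be reported as finding the delayed strategy inferior. The article says recruitment is ongoing, so the rule can still be put right before the primary result is known. A correction made after such an interval had been seen would look post hoc.

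**Working it through.** **Inputs from the article**
- Margin −10 points (elective minus acute), 95% interval, one-sided alpha 0.025, power 90%, acute rate 90% (Sample size section).
- Equal allocation: "If patients were randomized into two equal groups, the total sample size would be 380 patients", so 190 per arm.
- Allocation "with a randomization ratio of 2:3", acute to delayed (Randomization).
- At least 190 acute patients, and "the elective CV treatment group (at least 285 patients"); 475 in total, raised to 500 for losses. At 2:3, 500 is 200 acute and 300 elective.
- Intention-to-treat is primary and per-protocol is a sensitivity analysis (Primary and secondary end-points).

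**Assumptions made here.** The true elective rate is 90% in the base case (not stated in the article). True differences of −3 points and acute rates of 80% and 85% are illustrative.

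**Step 1: reproduce the sample size.** n per arm = (1.960 + 1.282)² × (0.9×0.1 + 0.9×0.1) / 0.10² = 10.51 × 0.18 / 0.01 = 189.1, rounded up to 190; total 380, as stated. Then 190 × 1.5 = 285, 190 + 285 = 475, and 475 / 0.95 = 500. The design calculation is sound.

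**Step 2: an inconclusive result under the rule.** Take 180/200 acute (90%) and 255/300 elective (85%). The difference is −5.0 points.

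SE = √(0.90×0.10/200 + 0.85×0.15/300) = √0.000875 = 0.0296.

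95% interval = −5.0 ± 1.96 × 2.96 = −10.8 to +0.8 points. It contains −10% and 0, and the written rule returns *inferior*.

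**Step 3: how often the label is returned.** Let d be the true difference and SE its unpooled standard error, with the observed difference taken as normal.
- Written rule: P(lower bound < −0.10) = Φ((−0.10 + 1.96·SE − d)/SE).
- Also requiring the upper bound below 0: at these sizes this equals P(upper bound < 0) = Φ((−1.96·SE − d)/SE), because 1.96·SE exceeds 5 points.

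Worked case, 200 vs 300, d = 0: SE = √(0.09/200 + 0.09/300) = 0.0274. The written rule gives Φ((−0.10 + 0.0537)/0.0274) = Φ(−1.69) = 4.5%. The stricter rule gives Φ(−1.96) = 2.5%.

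| Acute vs elective | True difference | Written rule | Upper bound also below 0 | Excess (points, from unrounded values) |
|---|---|---|---|---|
| 200 vs 300 | 0 | 4.5% | 2.5% | 2.0 |
| 190 vs 285 | 0 | 5.5% | 2.5% | 3.0 |
| 190 vs 190 (per-protocol) | 0 | 9.9% | 2.5% | 7.4 |
| 200 vs 300 | −3 points | 31.8% | 18.0% | 13.8 |
| 190 vs 285 | −3 points | 34.0% | 17.3% | 16.7 |
| 190 vs 190 (per-protocol) | −3 points | 42.8% | 14.9% | 28.0 |

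**Step 4: check.** A simulation of 1,000,000 trials at 200 vs 300 with no true difference gave the label in 3.7% of trials, and in 1.3% with an interval that also reached 0 or above. The normal approximation therefore slightly overstates the excess in that case.

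**Step 5: dependence on the 90% assumption.** At 200 vs 300 with equal true rates, the written rule returns *inferior* in 13.4% of trials if both rates are 85% and in 21.8% if both are 80%, against 2.5% with the stricter rule.

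**The case against.** The strongest reply is that the primary inference is intact. The article fixes the margin, direction, interval, bound and alpha, and the success criterion (lower bound not below −10%) is the plain complement of the stated rule. Read against the trial's hypothesis, *considered inferior* may simply mean *not shown to be non-inferior*. The required interval would also show any reader that it contains 0. All of this stands as a limit on severity. It does not make the wording right, because no other text supplies the milder meaning or an inconclusive outcome.

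A second reply is that the two rules rarely disagree. With acute observed at 90% and 200 vs 300 patients, they differ only when elective is observed between about 84.1% and 85.7%. Below that range the upper bound is already under 0 and both rules say inferior. This also stands, and it is why the size is given as an excess over the stricter rule.

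A reader might infer more than the article supports:
- **That every missed margin becomes proof of harm.** The article says *considered*, not proved, and some missed margins do support inferiority.
- **That the whole type II error is a rate of false inferiority claims.** At 190 vs 190 with equal rates the label's 9.9% does match the design's 10% type II error, but 2.5 points of it would be labelled inferior under the stricter rule too. A true −3 is also not a false claim if inferior means a difference below 0.
- **That the test or sample size is faulty.** Step 1 shows otherwise.

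**Conclusion.** The rule is wrong as written, and the severity is minor. It equates failure to show non-inferiority with inferiority and provides no inconclusive outcome.

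If both strategies are truly at 90%, the wording adds about 2 to 3 points to the chance of an *inferior* label in the primary intention-to-treat analysis, and about 7 points in the per-protocol sensitivity analysis if one-third of the elective arm is excluded. At an assumed true difference of −3 points, inside the margin the article accepts, the intention-to-treat excess is about 14 to 17 points.

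These figures rest on the normal approximation and the 90% acute rate; a lower rate would enlarge them. Any claim of non-inferiority, its one-sided 0.025 error rate and the totals of 380, 475 and 500 are unaffected.

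**What to change.** Replace the decision sentence with:

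*Non-inferiority is concluded if the lower bound of the two-sided 95% CI for elective minus acute is above −10 percentage points; otherwise non-inferiority is not demonstrated. The elective approach is called inferior only if the upper bound is below 0.*

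In the same edit, reword the preceding sentence so that power refers to showing non-inferiority when the elective approach is not worse by the margin.

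The cost is a wording change in the protocol, carried into the analysis plan. Conduct, recruitment, sample size, alpha and analysis sets do not change. It should be dated before the primary result is known.

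### Randomization is blocked by site, but the comparisons described use neither site nor baseline arrhythmia factors: the interval is valid, slightly conservative, and could be sharpened at no cost

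*Protocol article*

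**What the plan says.** Under Randomization, patients are allocated to acute or delayed cardioversion "with a randomization ratio of 2:3". The same section says: "Randomization is performed in site-specific blocks with the intention of balancing patient randomization" where a centre recruits few patients. Overall design names three centres.

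Sample size calculations and considerations gives the decision rule. The delayed strategy is inferior if the "lower bound of the 95% confidence interval for the difference in sinus rhythm prevalence", elective minus acute, falls below −10%. The margin is justified there too: "A 10% margin in sinus rhythm prevalence between the treatment groups is deemed clinically acceptable". The sizing uses 90% sinus rhythm in the control arm, one-sided alpha 0.025 and 90% power.

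The closing paragraph of that section covers methods in general. It says χ² "testing is used to compare the distributions of categorical variables", with t-tests or non-parametric tests for continuous variables. It does not mention site or covariates, and does not refer back to the decision rule.

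Overall design admits first or repeated, paroxysmal or persistent, AF or AFL. Data collection and follow-up describes a verified medical history for every patient.

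**The concern.** Blocking within site forces the arms to be nearly balanced at each centre. Differences in sinus rhythm rate between centres then add almost nothing to the sampling error of the treatment difference. A standard error computed as if the 500 patients came from one unblocked pool still counts that between-centre variation, so the interval is wider than the design warrants. The same holds for baseline factors that predict rhythm at 4 weeks: if they are recorded and left out, precision is given away.

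A smaller matter of wording comes with this. The primary end-point is binary, and the methods paragraph assigns categorical variables to χ² without exception. A χ² test of equality and the confidence-interval rule answer different questions and can point in opposite directions, so the plan should say which one governs the primary end-point.

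At stake are a little precision in the interval that decides the trial, most of all in the smaller per-protocol set, and clear reporting. Validity is not at stake.

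**Working it through.** **1. The plan's own figure.** Inputs from Sample size calculations and considerations: control rate 0.90, margin 0.10, one-sided alpha 0.025, power 0.90. The same rate in the delayed arm is assumed here.

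n per arm = (1.960 + 1.282)² × 2 × 0.90 × 0.10 / 0.10², rounded up to 190, so 380 in total. Then 190 / (1 − 1/3) = 285; 190 + 285 = 475; and 475 / 0.95 = 500. All stated figures reproduce. The trial is sized for an unstratified risk-difference comparison against the margin.

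**2. Ignoring site: simulation.** 200 v 300 patients, three sites, 40,000 replicates per scenario. Assumptions, not in the document: site shares 60/20/20% and the site rates shown. The stratified analysis uses Mantel–Haenszel weights. Each cell gives unstratified v stratified.

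| Site rates | Type I error at a true difference of −10 points | Power at a true difference of 0 |
|---|---|---|
| 90/90/90% | 2.3% v 2.4% | 96.2% v 96.3% |
| 95/90/85% | 2.2% v 2.5% | 98.8% v 98.8% |
| 97/85/80% | 2.0% v 2.5% | 98.2% v 98.5% |

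The unstratified interval stays below the nominal 2.5%. It loses at most about 0.3 points of power.

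**3. Share of variance explained.** R² = 1 − Σ w·p(1−p) / [p̄(1−p̄)], with assumed rates:
- Site, weights 0.50/0.25/0.25: rates 85/90/95% give 1.7%; rates 80/90/95% give 3.6%.
- One binary factor: 80% v 95% in shares 0.33/0.67 gives 5.6%; 70% v 95% in shares 0.20/0.80 gives 11.1%.

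**4. Effect on the interval.** At 90% in both arms and 200 v 300, the half-width is 1.96 × √(0.09/200 + 0.09/300) = 5.4 points. Multiplying by √(1 − R²) narrows it by about 0.05–0.1 point for site and by up to about 0.3 point at R² = 11.1%.

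**5. Effect on power.** Power = Φ(0.10/SE − 1.96), with SE multiplied by √(1 − R²) after adjustment (an approximation).
- 190 v 190, the per-protocol size if one-third of 285 are excluded: SE = √(2 × 0.09/190) = 0.0308, power 90.1%. R² = 5.6% gives 0.0299 and 91.7%; R² = 11.1% gives 0.0290 and 93.1%.
- 200 v 300, all randomized: SE = 0.0274, power 95.5%. The same two values of R² give 96.4% and 97.2%.

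**6. χ² against the decision rule.** Illustrative counts (acute v delayed), uncorrected χ², Wald interval:
- 180/200 v 255/300: p = 0.10, interval −10.8 to +0.8 points. No significant difference, yet non-inferiority is not shown.
- 192/200 v 273/300: p = 0.03, interval −9.2 to −0.8 points. Significantly lower, yet non-inferiority is met.

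In both cases the stated interval rule gives the right answer to the trial's question, and the χ² p-value does not.

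**The case against.** The strongest reply has three parts.

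First, the article already fixes the primary decision by a confidence interval for the risk difference. The χ² sentence sits in a generic paragraph that mentions neither the primary end-point nor non-inferiority. This stands. A reader who sees only the methods paragraph might infer that χ² is the sole comparison for the binary primary end-point and that the margin is never tested. The article does not support that reading: the −10% rule is stated in the same section and the sample size matches it.

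Second, this is a condensed article. Site adjustment, interval method and covariates commonly belong in the full protocol or SAP, which are not at hand. The article does not say that the interval will ignore site. This also stands, so the silence is not counted as an error. What remains is that the methods described do not use the blocking, and a better specified interval is available.

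Third, the effect is small and conservative, and the larger figures come from assumed prognostic factors. This is correct as well. The document gives no sinus rhythm rates by centre, arrhythmia type or episode history, and randomization is not described as stratified by the last two. Leaving those covariates out breaks no design feature. The objection limits the grade of the point but does not remove the gain.

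**Conclusion.** The point holds as a modest, cost-free improvement. The decision rule is sound and tests the margin directly. As described, the comparisons use neither the site blocking nor baseline arrhythmia factors, so the interval is slightly wider than it needs to be.

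The cost of leaving out site is at most about 0.3 points of power in the scenarios simulated, with type I error below nominal. Adjusting for a factor that explains about 6–11% of variance would add roughly 2–3 points of power at 190 v 190 and 1–2 points at 200 v 300. All these sizes rest on assumed rates and site shares. A reader might infer that unstratified analysis endangers the trial's conclusion. The figures do not support that, since the loss is small and on the conservative side.

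**What to change.** State in the analysis text:

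1. The primary analysis is the 95% confidence interval for the difference in sinus rhythm prevalence, elective minus acute, with its lower bound compared with −10%. Name the method: either stratified by site (Mantel–Haenszel weights with a stratified Miettinen–Nurminen interval), or standardized to a risk difference from a logistic model with site, AF v AFL and first v recurrent episode. Use the same method for the per-protocol sensitivity analysis.
2. χ² tests apply to secondary categorical comparisons and play no part in the non-inferiority decision.

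The cost is a few sentences; sample size and data collection do not change. The article describes recruitment as ongoing and allocation as unblinded, so the choice should be fixed before outcomes are compared by arm. If the SAP already specifies such an analysis, it is enough to confirm that and align the article's methods paragraph.

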## Discussion

Early CV in the ED has long been the standard approach to managing recent-onset AF/AFL. However, given the high recurrence rate of AF and the growing number of affected patients, this strategy places a significant burden on emergency services, where resources are often stretched and patient turnover is high.^1–3,5^ The AFFELECT trial introduces a novel approach to the management of acute AF/AFL by challenging the long-standing practice of immediate rhythm control in the ED.

The AFFELECT trial proposes that rhythm control can be safely deferred for 5–9 days in clinically stable patients, shifting care from the ED to elective cardiology units. This approach allows for spontaneous conversion in many cases^16^ and facilitates a more measured, patient-centred decision-making process regarding CV. The clinical comparison focuses on overall sinus rhythm prevalence at 4 weeks and the total number of CV procedures required to achieve this outcome in each strategy. This reflects the real-world decision faced in the ED and promotes a more individualized, resource-conscious, and clinically deliberate pathway that better aligns with practical clinical management.

Treating haemodynamically stable patients in dedicated elective cardiology units rather than crowded EDs could offer several advantages. It may substantially reduce the number of CVs performed, lower healthcare costs, and prevent repeated unnecessary ED visits. Moreover, concentrating the management of these patients in specialized cardiology settings enables more structured follow-up, coordinated decision-making, and comprehensive rhythm control strategies, which are associated with a reduction of morbidity and mortality in selected patients.^26^ If successful, this paradigm could meaningfully redefine the standard of care for acute AF/AFL, aligning patient safety, clinical efficiency, and sustainable healthcare delivery.

## Conclusion

The AFFELECT trial will demonstrate whether the delayed approach of rhythm control in recent-onset AF or AFL is non-inferior compared to standard treatment with respect to long-term maintenance of sinus rhythm. In this scenario, the number of ED visits and CV procedures could decrease significantly, alleviating the burden on emergency services, while directing the treatment of AF/AFL patients to specialized units focused on AF and AFL care.

## Data Availability

Data will be made available upon reasonable request to the chief investigator, subject to applicable data protection regulations and pending the approval of the study steering committee.
